### Assessment of outcome

The primary outcome will be change from baseline in the NIH-CPSI, a validated instrument used for the assessment of men with CP/CPPS (see Figure 1) [8]. The NIH-CPSI assesses domains of pain, urinary function, sexual function, and the impact of symptoms on quality of life.

Secondary outcomes will include the SF-36, HAD (Hospital Anxiety and Depression) scale and PAM (Patient Activation Measurement) tool. The SF-36 will provide a measure of generic quality of life. The HAD scale is a self-screening questionnaire for depression and anxiety. The PAM tool will provide a measurement of empowerment and be used to evaluate the degree to which patients feel that they are in control of their health status. Changes in analgesic and drug requirement will be a secondary effectiveness outcome. An economic evaluation will also be undertaken as a secondary outcome measure.

### Intervention

The intervention comprises a total of six consecutive once-weekly cognitive behavioural therapy sessions delivered to small groups (5-8) of men with CP/CPPS. Each session will last 2 hours and will be led by a Consultant Clinical Psychologist with support from a Specialist Pain Nurse. There will be further input from a Consultant Pain Specialist and Senior Urologist if required particularly in the initial sessions. The sessions will focus on re-enablement through patient education, identifying and challenging negative thoughts, fostering a sense of control and introducing problem-solving and goal-setting strategies. The content of each session is briefly detailed in Table 2.

**Table 2 T2:** Group-directed CBT health improvement intervention

	Content	Aim
*Week 1*	Introduction to programme. Ice-breaking exercise Information on CPPS (Consultant Pain Specialist) Set goals	Facilitate group to bond. Validates pain experience Promote re-engagement with valued activities
*Week 2*	Education re Gate Control Theory Identify gate openers Review goals Homework re goals Homework re gate closers	Validate pain experience Foster a sense of some control Increase valued activities/quality of life
*Week 3*	Education re Hot Cross Bun (CBT) Introduce Thought Records Homework: complete Thought Records	Introduce cognitive behavioural Principles Begin to identify automatic thoughts
*Week 4*	Thought Records Homework: complete Thought Records	Identify automatic thoughts and unhelpful behavioural response. Link to emotional state
*Week 5*	Challenging Thoughts Homework: Thought Challenging	Challenge unhelpful thoughts. Identify more appropriate thoughts Problem-solving strategies
*Week 6*	Communication Skills	Problems solving strategies Identify and reduce solicitous behaviour

A programme of group-directed cognitive behavioural therapy designed  specifically for men with CP/CPPS.

All patients randomised to the intervention arm will be able to leave the study at any time and all will be offered standard pain clinic care thereafter. We will carry out both intention to treat and per protocol analysis.

### Data Collection, Management and Analysis

Data will be collected and managed by a Specialist Research Nurse. The Specialist Research Nurse will be responsible for the day-to-day running of the trial as well as the collection of all administrative, demographic and outcome data. She will be the key contact for participants requiring support or advice throughout the study.

Outcome data will be collected at the time of enrolment into the study and again at 2, 6 and 12 months reviews after the commencement of treatment as part of a routine outpatient pain clinic review. The Specialist Research Nurse responsible for collecting these data will not be aware which treatment each patient has received.

### Statistical analysis

First descriptive and demographic statistics will be presented at baseline and follow-up measurements including measures of locations, for example mean or median and measures of spread including standard deviations or interquartile range depending on the distribution of measurements. Further, percentages and the 95% confidence intervals will be given for categorical data stratified by treatment group. All statistical tests will be carried out using two-sided tests at 5% significance level.

Given the repeated nature of our study, we will use the analysis of covariance approach recommended by Frison and Pocock for which the follow-up measurements are analysed at each follow-up time point adjusting for baseline and other confounding factors [9].

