**Methods/Design:**

Men will be recruited from general urology outpatient clinics following the exclusion of other diagnoses that could be responsible for their symptoms. Men will be randomised to attend either a self management healthcare and education programme or to pain clinic referral alone. The self management programme will be administered by a clinical psychologist to small groups of men over six consecutive weekly sessions each lasting two hours. Patients will be taught techniques of problem-solving and goal-setting and will learn coping mechanisms and how to modify catastrophic cognition.

The primary outcome will be change from baseline in the National Institute of Health Chronic Prostatitis Symptom Index, a validated instrument for the assessment of men with chronic prostatitis. Secondary outcomes include generic quality of life scores and analgesic and drug usage. Outcomes will be assessed at 2, 6 and 12 months.

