### Power Calculation

This is based on the primary outcome measure, the National Institute of Health Chronic Prostatitis Symptom Index (NIH-CPSI, see Figure 1). Mean NIH-CPSI scores in published trials are around 25, with standard deviation in the region 6-7. To detect a mean fall in NIH-CPSI of 4 points, we used CPSI score in control of 25.2, and CPSI score of 21.2 in the intervention with standard deviations of 6.1 and 7.2 in the control and intervention respectively. At 90% power, 5% two sided significance level, we estimate a sample size of 59 individuals in each group. Taking account of 15% loss to follow-up, we will require 60 individuals in each group giving a total sample size of 120.

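### The primary outcome has no primary time point but is tested separately at 2, 6 and 12 months, each at 5%; if any one visit can count as success, the two-sided error exceeds 5%

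*Protocol article*

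**What the plan says.** Under Assessment of outcome, the article states: "The primary outcome will be change from baseline in the NIH-CPSI". No visit is attached, and the abstract and the Power Calculation section do not supply one either.

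The abstract adds: "Outcomes will be assessed at 2, 6 and 12 months". Data Collection, Management and Analysis confirms that data are collected at enrolment and "again at 2, 6 and 12 months reviews after the commencement of treatment". The visits are not ranked.

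Under Statistical analysis, the method is an analysis of covariance in which "the follow-up measurements are analysed at each follow-up time point adjusting for baseline and other confounding factors". The same section sets the level: "All statistical tests will be carried out using two-sided tests at 5% significance level".

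The Power Calculation describes one comparison at an unnamed time: "To detect a mean fall in NIH-CPSI of 4 points, we used CPSI score in control of 25.2", with 21.2 in the intervention arm, and "standard deviations of 6.1 and 7.2 in the control and intervention respectively". It concludes: "At 90% power, 5% two sided significance level, we estimate a sample size of 59 individuals in each group".

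The article states no deciding visit, order of testing, requirement that all visits succeed, summary over time or adjustment for multiple tests.

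**The concern.** The trial is sized for one test at 5%, but the analysis section sets up three tests of the primary outcome, each at 5%. With no visit designated, a reader of the results cannot tell which of the three was meant to settle the question, and the trial team is not bound to one.

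The choice of visit also changes the clinical question. The Study Plan places the first follow-up questionnaire at the end of week 7, when the last session has just finished, and the final one at week 57. A benefit at the end of treatment and a benefit a year later are different claims. As written, an effect present only at the first visit could be presented as meeting the main objective, and so could one seen only at the last. The Dissemination section expects the result to bear on the standard of care, so the error rate behind a positive claim matters.

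**Working it through.** **Inputs from the article.** Means 25.2 and 21.2 (difference 4); standard deviations 6.1 and 7.2; two-sided 5%; 90% power; 59 per arm (Power Calculation). Three follow-ups (abstract; Data Collection, Management and Analysis). One test per follow-up, each at two-sided 5% (Statistical analysis).

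**Assumed, because the article does not give it.** The correlation r between the three test statistics, taken as equal for all pairs and varied over a range.

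**Step 1: reproduce the sample size.** n per arm = (1.960 + 1.282)² × (6.1² + 7.2²) / 4² = 10.507 × 89.05 / 16 = 58.5, rounded up to 59. This matches the stated figure, so the calculation covers exactly one comparison at 5%, with no allowance for three.

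**Step 2: error rate if any one visit counts as success.** With independent tests, the two-sided rate is 1 − 0.95³ = 14.26%, and the rate in the direction of superiority is 1 − 0.975³ = 7.31%. For correlated tests, the probabilities that at least one |Z| exceeds 1.96, or at least one Z exceeds 1.96, were found by numerical integration over a trivariate normal distribution with equal correlations. Simulation with 4 million draws gave the same two-sided values to within 0.05 percentage points.

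| r | Any visit, two-sided | Any visit, false superiority |
|---|---|---|
| 0 | 14.26% | 7.31% |
| 0.4 | 13.15% | 6.58% |
| 0.5 | 12.54% | 6.27% |
| 0.6 | 11.81% | 5.91% |
| 0.7 | 10.92% | 5.46% |
| 0.8 | 9.82% | 4.91% |
| 0.9 | 8.36% | 4.18% |
| 1 | 5% | 2.5% |

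**Step 3: which correlations are plausible after baseline adjustment?** If follow-ups correlate f with each other and b with baseline, the adjusted correlation is (f − b²)/(1 − b²).

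- If f = b = 0.5, this is 0.25/0.75 = 0.33, and the two-sided rate is 13.4%.
- If f = b = 0.9, it is 0.09/0.19 = 0.47, and the rate is 12.7%.
- If f = 0.7 and b = 0.5, it is 0.45/0.75 = 0.60, and the rate is 11.8%.

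An assumed range of 0.4-0.8 is therefore reasonable, but it remains an assumption.

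**Step 4: the opposite rule.** If all three visits had to be significant, the two-sided error would be 0.32%, 0.55%, 0.89% and 1.41% for r = 0.5, 0.6, 0.7 and 0.8, well below 5%. The unstated success rule thus moves the error rate from under 2% to over 12%.

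**Step 5: what correction instead of designation would cost.** Bonferroni over three visits gives 0.05/3 = 0.0167 per test, with critical value 2.394. Then n = (2.394 + 1.282)² × 89.05 / 16 = 75.2, or 76 per arm; with 15% loss, 76/0.85 = 89.4, or 90 per arm. Keeping 59 evaluable per arm, 4/√(89.05/59) = 3.256, and power is Φ(3.256 − 2.394) = 81% instead of 90%.

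**The case against.** The strongest reply is that the article never says significance at any one visit would be success. Its statement on significance sets the level of each test and makes no claim about a familywise rate, so no false error rate has been asserted. That is right. The sentence is incomplete as a decision rule; it is not a wrong statement of an overall error rate.

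A reader might also infer that the trial's false-positive rate simply is about 10-12%. The documents do not support that as a flat figure. It needs an any-visit rule and a correlation of roughly 0.57-0.79, and neither is stated. The two-sided figure also counts false results against the programme, so the risk of a wrong superiority claim is about half as large.

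A further tempting step is to count the intention-to-treat and per-protocol analyses separately and speak of six primary tests. The article says only that both will be done. Nothing makes a significant result in either one a route to success, so that count is unsupported.

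Finally, this is a condensed article, and multiplicity handling often sits in an analysis plan that is not shown here. That limits how firmly one can say that no rule exists anywhere. It does not remove the point. The visit is part of the definition of the primary outcome, and the article goes beyond silence by prescribing separate 5% tests at each visit.

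**Conclusion.** The point stands in conditional form. The primary outcome has no primary time point, the analysis section tests it three times at two-sided 5%, and the sample size assumes one such test. If significance at any one visit counted as success, the two-sided familywise error would be about 10-13% for assumed correlations of 0.4-0.8 and about 14% under independence. False superiority would be about 5-7%, against a nominal 2.5%. With equal, non-negative correlations, every value short of perfect correlation exceeds the nominal level. Under an all-visits rule the error would instead be below 5%. The defect is that the article does not say which rule applies; no single inflated figure can be attributed to the trial.

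**What to change.** Before any outcome data are compared between arms, name one primary endpoint, tested at two-sided 5%. Either of these would do:

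- the NIH-CPSI total score at one visit chosen by the sponsor, adjusted for baseline; or
- one test on the mean of the three follow-up scores, adjusted for baseline.

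Under the first option, report the other two visits as secondary; under the second, report all three individual visits as secondary. State in the Power Calculation that the 4-point difference and the standard deviations refer to the chosen endpoint, and make the abstract, Assessment of outcome and Statistical analysis sections agree with it.

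This is a small change of wording in four places. With one named visit the type I error is 5%, and 59 per arm before loss to follow-up stands if the assumed difference and standard deviations apply at that visit. With the mean of the follow-ups, those assumptions should be restated for that average. The downside is that significance at another visit alone would no longer count as the primary result. Keeping all three visits as co-equal primary tests with Bonferroni correction would instead need 76 per arm before loss, or accept about 81% power at 59.

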### Randomisation methods

Randomisation will be carried out by a method of Random Permuted Blocks so as to ensure exact equal treatment numbers at certain equally spaced time points in the sequence of patient assignments. The randomisation sequence will be generated using statistical software in random blocks, size of four individuals per block.

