**Departmental Costs**
Room Hire for therapy sessions - 2 hourly sessions, 10 individual groups, 1 session per week for 8 weeks per group. (60 participants) £15.91per hour (£2,546)
Refreshments for group sessions (60 participants) £40.00 per patient (£2,400)
Research Assessment Room Hire: 4 appointments × 45 mins for 120 participants £15.91 per hour (£5,728)

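### CBT is given in about ten therapy groups, but the sample size and the named ANCOVA treat all men as independent; if outcomes correlate within groups, the standard error is too small

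*Protocol article*

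**What the plan says.** The Intervention section of the protocol article describes "six consecutive once-weekly cognitive behavioural therapy sessions delivered to small groups (5-8) of men with CP/CPPS". Table 4, under Departmental Costs, budgets for "10 individual groups, 1 session per week for 8 weeks per group" and 60 participants, so the mean group size is 6. (The weeks in that costing line and the number of sessions in the Intervention section differ. The two places must be reconciled, but this does not affect the point here.) The comparator in the Abstract is pain clinic referral alone, and no group format is described for it.

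Allocation is of individuals, in "random blocks, size of four individuals per block".

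The Power Calculation section states its inputs: "we used CPSI score in control of 25.2, and CPSI score of 21.2 in the intervention with standard deviations of 6.1 and 7.2". It concludes: "At 90% power, 5% two sided significance level, we estimate a sample size of 59 individuals in each group". No ICC, group size or design effect appears.

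The Statistical analysis section adopts analysis of covariance, in which "the follow-up measurements are analysed at each follow-up time point adjusting for baseline and other confounding factors".

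**The concern.** This is a partially nested design: one arm is clustered by therapy group and the other is not. Shared group experience is part of the treatment. Table 2 sets group cohesion as an aim of week 1, and goals are reviewed in later sessions. Men in one group may therefore end up more alike than men in different groups.

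An analysis that counts 60 CBT men as 60 independent observations then understates the variance of the CBT mean. The confidence interval for the primary comparison is too narrow and p-values are too small. The article's main objective is to show that CBT is more effective, so an inflated false-positive rate bears directly on its conclusion. The reference to other confounding factors does not cover this. Therapy group arises after randomisation and in one arm only, so it is not a confounder.

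**Working it through.** **Inputs.** Difference 4 points (25.2 v 21.2), SD 6.1 control and 7.2 CBT, two-sided 5%, 90% power, 60 per arm (Power Calculation). Mean group size m = 6 (Table 4: 60/10). The ICC is not in the article; 0.01 to 0.10 is assumed here.

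**1. Reproduce the plan's figure.** With independent men, n = (1.960 + 1.2816)² × (6.1² + 7.2²) / 4² = 10.507 × (37.21 + 51.84) / 16 = 58.48, rounded up to 59. This is the stated number, so it contains no hidden allowance for clustering.

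**2. Add clustering in the CBT arm only.** The design effect is DE = 1 + (m − 1) × ICC, and Var(difference) = [6.1² + 7.2² × DE] / n. At ICC 0.05, DE = 1.25 and the variance with 60 per arm is (37.21 + 64.80)/60 = 1.700, so SE = 1.304. Under independence it is 89.05/60 = 1.484, so SE = 1.218. The ratio is 1.070.

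**3. Type I error of an analysis that ignores groups.** The formula is 2 × [1 − Φ(1.960 / SE ratio)]. Power for 4 points is Φ(4/SE − 1.960).

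| ICC | DE | SE ratio | Type I error | Power, 60 analysed per arm | n per arm for 90% |
|---|---|---|---|---|---|
| 0 | 1.00 | 1.000 | 5.0% | 90.7% | 59 |
| 0.01 | 1.05 | 1.014 | 5.3% | 89.9% | 61 |
| 0.02 | 1.10 | 1.029 | 5.7% | 89.1% | 62 |
| 0.05 | 1.25 | 1.070 | 6.7% | 86.6% | 67 |
| 0.10 | 1.50 | 1.136 | 8.5% | 82.4% | 76 |

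Power and n are for the unadjusted comparison that the article itself used, before any loss to follow-up.

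**4. Simulation.** With 10 groups of 6 against 60 controls and at least 40,000 runs per setting, a t-test ignoring groups rejected a true null in about 5.3%, 5.7%, 6.9% and 8.5% of runs at ICC 0.01, 0.02, 0.05 and 0.10. Repeat runs at 0.05 gave 6.6-6.9%. A test on group means with Satterthwaite degrees of freedom held about 5%. Its power with 60 per arm was about 87%, 86%, 83% and 78%. At ICC 0 it was already 88%, so about two points of that loss come from having only ten groups to estimate the variance.

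**5. Baseline adjustment.** Suppose the correlation of baseline with outcome is 0.5 (assumed; none is stated) and the group effect arises after baseline. Residual variances are multiplied by 0.75 and the residual ICC becomes 0.05/0.75 = 0.067. The variance is [0.75 × 37.21 + 0.75 × 51.84 × (1 + 5 × 0.067)]/60 = (27.91 + 51.84)/60 = 1.329, giving power of about 93%. The SE ratio is √(79.75/66.79) = 1.093, giving type I error of about 7.3%. Adjustment can therefore recover power, but it does not correct the error rate.

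**The case against.** **The ICC is assumed.** At 0.01-0.02 the type I error stays below 6%, which few would act on. The article describes sessions led by a Consultant Clinical Psychologist with set weekly content. If one person leads every group, one usual source of clustering is absent. This stands as a limit on size. It does not remove differences in group composition and dynamics, and the direction of the error is the same for any positive ICC.

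**The planned analysis is ANCOVA, so unadjusted power is not its power.** This stands. A reader might infer that clustering takes the trial below 90% power. The article does not support that without a baseline correlation, and at 0.5 (assumed) with ICC 0.05 power would be about 93% with 60 analysed per arm.

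**The shortfall looks larger after attrition.** A reader might quote power at 51 per arm, which is 60 less 15%, as the cost of clustering. That mixes in a different error. The article says "Taking account of 15% loss to follow-up, we will require 60 individuals in each group giving a total sample size of 120", whereas 59/0.85 gives 70. At ICC 0, 51 per arm already give only 85.7%, so that fall is not due to clustering.

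**The article is condensed, and an analysis plan not shown may add a group term.** This is possible, and it softens the point on the model. It does not change the sample size, which the article fixes and which was derived with no clustering.

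**Conclusion.** The point holds conditionally. The design is partially nested, 59 per arm reproduces only at ICC 0, and the analysis as named has no place for therapy group. If the ICC is above zero, the planned standard error is too small and the 5% level is exceeded: slightly at ICC 0.01-0.02, and by roughly 2 to 3.5 percentage points at 0.05-0.10. These figures assume 10 equal groups of 6 and 60 individually treated controls.

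The stronger statement, that the stated error rate and power definitely fail, is not supported, because the article gives neither an ICC nor a baseline correlation. On its own unadjusted basis, power is about 87% or 82% by formula at ICC 0.05 or 0.10. For a group-respecting test with small-sample degrees of freedom it is about 83% or 78%. Baseline adjustment could make up this loss by an amount that cannot be fixed from the article.

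**What to change.** - **Primary model.** Use a mixed model with baseline NIH-CPSI and arm as fixed effects, a random therapy-group effect in the CBT arm only, arm-specific residual variance, and Satterthwaite or Kenward-Roger degrees of freedom. Under intention to treat, enter each control man, and each CBT-arm man who never joins a group, as his own cluster.
- **Data.** Record the therapy group of each CBT man as the groups run. The identifier reveals allocation, so hold it in a file apart from the Specialist Research Nurse, who is to be unaware of treatment (Data Collection, Management and Analysis).
- **Power statement.** Restate it over an assumed ICC range, for example 0.01-0.10, with mean group size 6, and say whether baseline adjustment is counted. This asks for an honest statement of power, not for higher enrolment. Deal with the 15% loss separately.

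The cost is one variable, a separately held file and a few lines of text. The price in results is a wider confidence interval and a lower stated power.

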### Resource Requirements

This study will require additional resources from the Norfolk and Norwich University Hospital NHS Foundation Trust. These include the involvement of a number of health care professionals in the provision of the healthcare intervention. A Specialist Research Nurse will also be required to co-ordinate the study and to collect data on effectiveness outcomes. Funding will be required for room hire and refreshments for the participants. Administrative expenses and licence fees for the validated instruments to assess outcomes constitute further costs.

These costs will be met entirely through funding from the NHS East of England Regional Innovation Fund (see Table 4).

**Table 4 T4:** Breakdown of study costs

